## Abstract

**Background:**

Prenatal anxiety affects between 20% and 30% of pregnant people and is associated with adverse prenatal health conditions, birth outcomes, and postpartum mental health challenges. Individuals from racial and ethnic minority groups, sexual and gender minority groups, and those with low income are all at heightened risk for prenatal anxiety due to disproportionate exposure to adverse social determinants of health. Digital cognitive behavioral therapy (dCBT) has been shown to reliably reduce anxiety in mostly White and middle- to higher-income samples, but its efficacy in low-income and marginalized pregnant people is understudied.

**Objective:**

We propose a randomized controlled trial of a dCBT (Daylight app, Big Health, Ltd) in a sample of low-income pregnant people oversampled for racial, ethnic, sexual, and gender minority identity.

**Methods:**

Participants (N=132) will be randomized to the intervention or waitlist control group using a 1:1 allocation ratio. The intervention will be a self-guided application that uses an online therapist to teach and encourage the practice of 4 key cognitive behavioral therapy skills (eg, identifying catastrophic thinking and increasing physical relaxation) that can reduce anxiety. The primary outcome will be generalized anxiety symptoms; secondary outcomes will include depressive symptoms, stress, pregnancy-specific anxiety, and insomnia symptoms. Focus groups with a subset of participants will provide qualitative data about the acceptability of dCBT.

**Results:**

Recruitment began in June 2024. Data will be analyzed using linear mixed models, which will be fit with treatment condition (dCBT and waitlist control group) as the between-group factor, time (baseline, 3, 6, and 10 weeks post randomization) as a within-group factor, and a group-by-time interaction. Linear mixed models produce unbiased parameter estimates in situations where there are different numbers of observations per record and will accommodate intent-to-treat and sensitivity analyses.

**Conclusions:**

This clinical trial will evaluate the efficacy and acceptability of a self-guided dCBT for prenatal anxiety among low-income and marginalized pregnant people, a group that continues to experience substantial barriers to accessing in-person evidence-based psychotherapy.

**Trial Registration:**

ClinicalTrials.gov NCT06404450; https://clinicaltrials.gov/study/NCT06404450

**International Registered Report Identifier (IRRID):**

DERR1-10.2196/70627

## Introduction

Anxiety is common and consequential during pregnancy; globally, about 15% of pregnant people are diagnosed with an anxiety disorder, and 18%-25% of pregnant people self-report symptoms that surpass a clinical cutoff using a validated screener [1]. Symptoms of clinical anxiety include experiencing excessive worry, difficulty controlling worries, restlessness, irritability, and sometimes, physical symptoms, such as heart palpitations and dizziness [2]. Anxiety symptoms can be exacerbated by experiences common during pregnancy, which include poor sleep and managing uncertainties related to labor and delivery [3]. The COVID-19 pandemic had profound impacts on the prevalence rates of prenatal anxiety. Meta-analytic data showed that about 31% of pregnant people reported elevated anxiety symptoms during the COVID-19 pandemic compared to 22.4% before the pandemic, representing a 35% increase in prevalence [2,3]. Notably, increase in the rates of elevated prenatal anxiety and pandemic-related symptoms did not impact pregnant people equally. Elevations in symptoms of anxiety and comorbid symptoms like depression have persisted at higher rates in marginalized pregnant people, including those who are categorized as Black, Latinx, Indigenous, Asian and Pacific Islander, and lesbian, gay, bisexual, transgender, and queer (LGBTQ+), and in those with low income [4,5].

Elevated anxiety symptoms during pregnancy contribute to the risk of a host of adverse prenatal health conditions, birth outcomes, and postpartum mental health problems. For example, prenatal anxiety is prospectively associated with gestational hypertension, intrauterine growth restriction, and having a preterm birth [6,7]. Biological mechanisms, like dysregulation in the hypothalamic-pituitary axis leading to premature accelerations in placental corticotropin-releasing hormones and cortisol, and behavioral mechanisms, such as substance use and poor sleep help explain the relationship between prenatal anxiety and adverse birth outcomes [8]. Elevated anxiety is also associated with psychiatric comorbidities, including depression, insomnia, and suicidal ideation [9-11], which are more common in marginalized pregnant people and those with low income [4,5,12,13].

In addition to anxiety disorders and elevations in general anxiety symptoms, pregnant people also experience pregnancy-specific anxiety*,* an affective state of persistent worry surrounding a pregnant person’s prenatal health, delivery, the well-being of the baby, and future parenting [14]. Pregnancy-specific anxiety is estimated to affect between 14% and 19% of pregnant people [14,15] and appears to be uniquely predictive of adverse birth outcomes like preterm birth. For example, pregnancy-specific anxiety is related to smaller gestational age and lower birth weight after accounting for generalized anxiety disorders [16]. Further, it is estimated that women with high levels of pregnancy-specific anxiety are 1.7-2.5 times more likely to experience a spontaneous preterm birth than women without pregnancy-specific anxiety [17]. Unsurprisingly, pregnant people reported high rates of pregnancy-specific anxiety during the COVID-19 pandemic [18]—a time when practices in labor and delivery units were in flux, and people worried about what a COVID-19 infection might mean for their developing fetus. With respect to sociodemographic risk, greater pregnancy-specific anxiety has been linked with lower income, non-White race, and Latina ethnicity [19-21]. These patterns suggest that rising rates of clinical and pregnancy-specific anxiety may be contributing to worsening racial and ethnic, LGBTQ+, and socioeconomic disparities in adverse pregnancy outcomes and postpartum mental health. Given the high need and lack of representation of racial and ethnic minoritized, marginalized, and low-income people in randomized trials for perinatal anxiety to date, testing the efficacy and acceptability of accessible interventions that address clinical anxiety among these groups is warranted [22,23].

Therapist-delivered cognitive behavioral therapy (CBT) has been shown to be effective in treating anxiety among White nonpregnant [24] and pregnant populations [25]. However, the effects of CBT on pregnancy-specific anxiety are largely unknown, as most studies testing interventions for anxiety in pregnancy do not measure this subtype of anxiety [26]. Notwithstanding, cognitive behavioral interventions can improve biological and behavioral variables that link pregnancy-specific anxiety to adverse birth and postpartum outcomes. For example, cognitive behavioral interventions can reduce cortisol [27] and improve sleep [28] in pregnant people.

Despite the promise of CBT for elevated anxiety symptoms experienced during pregnancy, racial and ethnic minoritized, marginalized, and low-income pregnant people often encounter several barriers to accessing evidence-based treatment (eg, long waitlists, childcare issues, and challenges with transportation) [29]. Recent innovations have focused on addressing barriers to CBT by adapting it for automated, digital delivery. Digital CBT (dCBT) is efficacious for treating clinical anxiety in mostly White, higher socioeconomic status, pregnant [30], and nonpregnant populations [31]. While marginalized pregnant people report high satisfaction with digital therapy, very few dCBT trials have enrolled meaningful numbers of racial and ethnic minoritized or low-income pregnant people [32,33]. This study addresses the critical need to evaluate whether dCBT can be used to address clinical anxiety among racial and ethnic minoritized, marginalized, and low-income pregnant people, subgroups disproportionately impacted by anxiety during pregnancy.

Building on a previous efficacy trial of the same dCBT in nonpregnant adult women that evidenced large improvements in anxiety symptoms, and high levels of engagement and safety [31], the Transforming Health and Reducing Perinatal Anxiety through Virtual Engagement (THRIVE) study tests whether the dCBT Daylight (Big Health), is an efficacious and acceptable treatment during pregnancy among racial and ethnic minoritized, marginalized, and low-income people. The hypothesis of this trial is that participants randomized to Daylight will demonstrate significantly greater reductions in anxiety symptoms compared to a waitlist control group. We also expect that participants randomized to Daylight will report reductions in associated mental health symptoms, including depression, stress, pregnancy-specific anxiety, and insomnia.

## Methods

### Objectives

Study objectives are to (1) measure the impact of dCBT (Daylight) on anxiety symptoms in racial and ethnic minoritized, marginalized, and low-income pregnant people with elevated anxiety; (2) assess the acceptability of dCBT for addressing elevated anxiety and related symptoms among pregnant participants; and (3) identify barriers and facilitators to the adoption of dCBT for use by racial and ethnic minoritized, marginalized, and low-income pregnant people enrolled in public insurance (MediCal).

### Trial Design

#### Overview

This is a phase 1 randomized controlled trial (RCT) that tests the efficacy of dCBT (Daylight) for treating anxiety during pregnancy using a parallel group design. Study participants will be in the study from enrollment at 8-27 weeks gestation until 6-8 weeks after their expected date of delivery. All participants complete assessments of self-reported symptoms of generalized anxiety, depression, stress, pregnancy-specific anxiety, and insomnia at baseline, 3, 6, and 10 weeks following randomization, and at a follow-up time point between 6 and 8 weeks post partum. The study also includes focus groups with a subset of RCT participants following intervention receipt to evaluate the acceptability of dCBT.

#### Randomization and Blinding

As outlined in the study schema (Table 1), after completion of the study consent and enrollment survey, participants will receive an email informing them if they have been randomized to receive complimentary access to the Daylight app immediately (ie, intervention condition), or to receive access in 10 weeks (ie, waitlist control condition). If randomized to receive access immediately, they will receive instructions on how to download the app and start using it. If randomized to receive access to the Daylight app in 10 weeks, they will be sent instructions for downloading and starting to use the Daylight app 10 weeks later.

**Table 1 table1:** Modules included in the Daylight digital cognitive behavioral therapy app.

Intervention module	Brief description	CBT^a^ principle	Learning goals
Worry scheduling and worry time	Scheduling a specific time and pace to worry (Worry Scheduling), and then cycling through worrisome thoughts (Worry Time).	Stimulus control	Learn to associate worry with a designated time and space. Learn to delay worry until a designated time. Learn to tolerate worry without avoidance.
Tense and release	Tensing and releasing muscles with relaxation cues.	Applied relaxation	Increase awareness of tension. Increase awareness of the difference between tensed and relaxed muscles. Learn to reduce muscle tension.
Thought challenger	Identifying catastrophic or unhelpful thoughts and using challenge questions to develop new perspectives on these thoughts.	Cognitive restructuring (decatastrophizing)	Increase awareness of catastrophic and unhelpful thoughts. Learn to challenge catastrophic thoughts. Increase cognitive flexibility.
Worry exposure	Imagining the “worst case scenario” or feared outcome of a specific worry.	Imaginal exposure	Learn to tolerate emotions associated with feared outcomes. Facilitate cognitive reappraisal of feared outcomes. Facilitate habituation to fear response (ie, fear extinction).

^a^CBT: cognitive behavioral therapy.

This study is designed to enroll marginalized (Latinx; Black, Indigenous, and people of color; or LGBTQ+ individuals) individuals at a ratio of 2:1. To ensure that randomization is in keeping with our intention of equal representation across groups, we will use a 1:1 allocation ratio with blocked randomization of marginalized people and not. The randomization sequence will be generated by the study biostatistician. The randomization sequence and block sizes will be concealed from all other study team members and participants. Study team members will not be able to influence randomization. Once an eligible participant completes their consent and enrollment survey, unmasked study staff will reveal the allocation assignment and notify participants of their assigned condition. The principal investigator and any staff member involved in data analysis will be blinded to condition assignment. Although we cannot blind participants from condition assignment, allocation will occur after the participant has enrolled to avoid selection bias.

### Participants

#### Enrollment and Eligibility

This is a remote RCT overseen at the University of California, San Francisco, and pregnant people residing in California are eligible to take part. In addition to California residence, participants must meet the following eligibility criteria: (1) enrollment in MediCal, a California health insurance plan for low-income people; (2) currently between 8 and 27 weeks pregnant; (3) age 18 years or older; (4) able to speak in English; (5) ninth-grade levels of education or greater; (6) daily access to a web-enabled computer, smartphone or tablet; and (7) elevated anxiety symptoms as measured by a score of 10 or greater on the Generalized Anxiety Disorder- 7 Scale (GAD-7; [34]). Consistent with the original Daylight efficacy trial [31], participants who have received CBT treatment for anxiety in the last 12 months, those with a new or changed dose of prescription medication for anxiety, depression, or insomnia in the last 4 weeks, and those with a self-reported diagnosis of schizophrenia, psychosis, bipolar disorder, seizure disorder, and substance use disorder will be excluded. A recent head trauma or brain damage, or a serious physical health concern necessitating surgery or hospitalization in the last 6 months will also lead to exclusion from the study.

#### Sample Size

In total, 110 pregnant people with elevated anxiety symptoms will be randomized to one of 2 study arms. Based on a previous study wherein the response to the Daylight tool (by the GAD-7; [34]) at 10 weeks post randomization was normally distributed with a mean of 12.15 (SD 4.73) in the waitlist control, and a mean of 7.90 (SD 4.85) in the dCBT group [31], we expect that a sample of 55 experimental and 55 control participants should detect a true difference in the mean symptoms of experimental and control participants of –2.696 or 2.696 with 80% power. An additional 22 participants will be recruited (ie, a total of 132 enrolled) to account for attrition rates of 17%, the average rate of attrition of marginalized pregnant people enrolled in psychological intervention studies [35]. While we are powered to detect intervention effects at 2 posttreatment time points (6 weeks and 10 weeks following randomization), we do not have pilot data to estimate power at our postpartum time point. Estimates of an effect size in this perinatal pilot are challenging to calculate, as gestational age may vary widely at enrollment (8-27 weeks) resulting in a postpartum assessment that will be up to 36 weeks post treatment for those enrolling at 8 weeks and as early as 15 weeks post treatment for those enrolling at 27 weeks. Thus, treatment effects at the 7-week postpartum time point are exploratory, and we will rely on effect sizes to describe effects as opposed to *P* values.

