#### Analyses

To examine the efficacy of dCBT (Daylight) on generalized anxiety symptoms (primary outcome) and symptoms of depression, stress, pregnancy-specific anxiety, and insomnia (secondary outcomes) from baseline to 10 weeks post randomization, we will use LMMs. These LMMs will be fit with treatment condition (dCBT and waitlist control group) as the between-group factor, time (baseline, 3, 6, and 10 weeks post randomization) as a within-group factor, and a group-by-time interaction. LMMs maximize data use because they produce unbiased parameter estimates in situations where there are different numbers of observations per record, so long as data are missing at random. A model-based approach will be used to assess the potential impact of data missing not at random on our findings. Pattern mixture models will be used to identify missingness patterns (eg, differential attrition based on randomization group) and to stratify analysis by these patterns as needed [55]. All primary and secondary analyses will be conducted on all randomized participants using an intention-to-treat approach. Sensitivity analyses will also be conducted to test the effects of Daylight among participants who (1) download the app, (2) complete at least 2 modules, and (3) complete all 4 modules, mirroring planned analyses from the original Daylight efficacy trial [56]. Finally, dependent on sample size, exploratory moderation analyses will be conducted to test for differential intervention efficacy among subgroups of racial, ethnic, or sexual and gender minoritize. No interim analyses are planned.

Regarding the assessment of dCBT acceptability, focus groups will be transcribed for qualitative analysis. In line with implementation science frameworks, we will use rapid qualitative techniques for thematic network analysis [57] using NVivo (version 11.4.2; Lumivero) software. Following the identification of codes, the 4 raters will meet to discuss differences and similarities amongst codes to ensure consistency. Codes will be refined and discussed until consensus amongst raters is reached.

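### The Sample Size section gives 110 as the number randomized where the rest of the article implies 132, and its detectable difference of 2.696 does not follow from the SDs it quotes

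*Protocol article*

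**What the plan says.** On the number randomized, the article makes two direct statements.

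- Sample Size section: "In total, 110 pregnant people with elevated anxiety symptoms will be randomized to one of 2 study arms".
- Abstract, Methods: "Participants (N=132) will be randomized to the intervention or waitlist control group using a 1:1 allocation ratio".

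The Sample Size section then continues: "An additional 22 participants will be recruited (ie, a total of 132 enrolled) to account for attrition rates of 17" per cent. Under Randomization and Blinding, "allocation will occur after the participant has enrolled to avoid selection bias", and under Analyses, "All primary and secondary analyses will be conducted on all randomized participants using an intention-to-treat approach".

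On the detectable difference, the Sample Size section starts from the previous trial's GAD-7 results at 10 weeks, "a mean of 12.15 (SD 4.73) in the waitlist control, and a mean of 7.90 (SD 4.85) in the dCBT group". From these it concludes that 55 per arm can detect a true difference of minus 2.696 "or 2.696 with 80% power". It gives no other SD and no alpha.

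**The concern.** The two statements concern the same quantity and cannot both be true. Randomization and Blinding has staff reveal the allocation once consent and the enrollment survey are complete. Screening, verification and orientation all come before that. No step between enrollment and allocation could remove 22 people, so it is not possible that 132 enroll and only 110 of them are randomized.

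The figure matters because accrual is in progress (24 randomized by March 2025) and no interim analysis is planned, so the number randomized is the accrual target. Someone checking the final report against the article could not tell whether 110 randomized met the target or fell 22 short.

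The detectable difference matters because readers will use it to judge how informative a null result is. Here the stated inputs and the stated output disagree.

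**Working it through.** **Inputs from the article.** 55 per arm; SDs 4.73 (waitlist) and 4.85 (dCBT); prior means 12.15 and 7.90, a difference of 12.15 − 7.90 = 4.25; power 80%; attrition 17%; totals 110 and 132. **Assumed:** two-sided alpha of 5%. The article states none, but the plus-or-minus form of the difference implies two sides. The test is a two-sample comparison of week-10 means, with power from the noncentral t distribution on 2n − 2 degrees of freedom and noncentrality d / (SD × √(2/n)).

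**1. The attrition allowance.**
- 110 / (1 − 0.17) = 132.5, so 132 is right to within rounding.
- 132 × 0.83 = 109.6, about 110.
- 22 / 132 = 16.7%, about 17%.

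The inflation is therefore sound: 132 start and about 110 remain. The 110 is the number expected after attrition, not the number randomized.

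**2. The literal reading, 110 randomized.** 110 × 0.83 = 91.3 in total, or 45.65 per arm.

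| n per arm | SD | Power at 2.696 | Power at 4.25 | Difference detectable at 80% |
|---|---|---|---|---|
| 55 | 5.0 | 80.0% | 99.3% | 2.70 |
| 55 | 4.79 | 83.3% | 99.6% | 2.58 |
| 45.65 | 5.0 | 72.2% | 98.0% | 2.96 |
| 45.65 | 4.79 | 75.8% | 98.7% | 2.84 |

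**3. Reproducing 2.696.** The pooled SD is √((4.73² + 4.85²)/2) = 4.790. With 55 per arm the standard error is 4.790 × √(2/55) = 0.9135. The detectable difference at 80% power and two-sided 5% is then:

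- SD 4.73: 2.55
- pooled SD 4.79: 2.58 (2.56 by the normal approximation)
- SD 4.85: 2.61
- SD 5.0: 2.695

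None of the quoted SDs gives 2.696. Solving for the SD that does gives 5.001.

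Other alphas do not explain the figure. With the pooled SD, power at 2.696 is 75.0% at two-sided 0.025, 62.9% at two-sided 0.01 and 90.1% at one-sided 0.05. Exactly 80% would need a two-sided alpha of about 0.0375, which is not a conventional level. Using the numbers left after attrition from 110 (45 or 46 per arm) does not explain it either: the detectable difference is then 2.83 to 2.86.

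**4. Size and direction.** 2.696 − 2.582 = 0.114 points on a 0–21 scale, and 2.582 / 2.696 = 0.958, so the quoted SDs give a figure about 4% below the stated one. If the quoted SDs are right, 55 per arm has slightly more power than claimed.

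**The case against.** The strongest reply is that the section corrects itself. Shortly after the 110 it adds 22 for attrition and reaches 132, the arithmetic is right, and the Abstract confirms 132 randomized. On this view one sentence is loosely worded and the design is intact. That stands, and it is why this is a correction of stated figures and not a design fault. It does not make the sentence correct, because the section labels the number expected after attrition as the number randomized.

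A reader might infer that the trial will stop at 110 and be underpowered. The documents do not support that. No passage names 110 as the point at which accrual stops, and both the Abstract and the Sample Size section point to 132. Even if accrual did stop at 110, the loss of power shows at the minimum detectable difference, not at the effect the plan cites.

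On the SD, rounding 4.73 and 4.85 up to 5.0 would be a reasonable cautious choice, and a condensed article may leave the planning SD and alpha to the full protocol. This also largely stands. However, the article chose to print the inputs and the result together and to present one as based on the other, and as printed they do not agree. That an SD of 5.0 was used is an inference from the arithmetic and is not stated anywhere. It would be wrong to read the mismatch as a sign of insufficient power, because it runs in the conservative direction.

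**Conclusion.** The point holds as a moderate correction. The 110 in the Sample Size section is mislabelled: the article's own procedures and attrition arithmetic make 132 the number enrolled and allocated, and about 110 the number expected to remain. The power figures for 110 randomized show what the literal wording would cost. They are not a forecast for this trial.

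The detectable difference of 2.696 is not reproduced from the quoted SDs, which give about 2.58, or about 83% power at 2.696. This second error is small and conservative, and would be minor alone.

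The results rest on a two-sided alpha of 5%, on a simple two-sample comparison at week 10 (the planned mixed model may differ somewhat), and on attrition being equal in the two arms.

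**What to change.** 1. In the Sample Size section, state that 132 will be randomized (66 per arm) and that about 110 (55 per arm) are expected to provide a week-10 GAD-7 after 17% attrition, in agreement with the Abstract.
2. For the detectable difference, do one of two things. Either restate it as about 2.58 for a pooled SD of 4.79 at two-sided 5%, or keep 2.696 and state the SD (about 5.0, if that is what was used) and the alpha behind it.

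The cost is wording only. The planned 132, the analysis and the conduct of the trial are unchanged.
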